**Inclusion in analysis**
*

All participants with available data will be included in the day seven analysis. For the one month and three-month outcomes, all participants including those lost to follow-up or who die within the time period will be included in analysis.

*

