The feasibility study identified that only 15 of these 20 patients subsequently underwent therapeutic aspiration. This was because thoracic ultrasound (US) performed following enrolment demonstrated that there was insufficient fluid for a therapeutic aspiration or that the fluid was not amenable to drainage. Therefore, we altered the inclusion criteria to specify that patients must have an effusion demonstrated on thoracic US or computer tomography (CT) scan prior to enrolment. This change to the inclusion criteria will ensure that all enrolled patients will undergo therapeutic aspiration.

We plan to analyse data only on patients with a final diagnosis of an MPE because effusions from other causes usually resolve with treatment of the underlying cause and recurrence is not a problem. However, when patients attend for therapeutic aspiration, the final diagnosis may not be known. Of the 15 patients who underwent therapeutic aspiration in our feasibility study, 12 of them had a final diagnosis of malignancy. For the full study, we plan to recruit 200 patients in Phase 1 to include at least 150 with a final diagnosis of MPE and full primary outcome data.

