**Sample size and analysis plan**
*

Based on our feasibility data, we estimate we need to recruit 200 patients to have complete data available on 150 patients. The main reason for this is that approximately 20% of patients will turn out not to have MPE and therefore will not be eligible for inclusion in the final analysis. The primary outcome measure is at one week and is part of standard clinical care and therefore we anticipate that loss to follow-up, withdrawal rates and missing data will be minimal based on our feasibility data and previous trial experience. A further validation cohort of 40 patients will be recruited subsequently. Follow-up will be either by review of available medical records, telephone or clinical appointment (if patient is coming up to hospital anyway) at 30 days and three months.

A sample size of 150 participants would allow us to have a shrinkage factor of 0.95, which is above the recommended 0.9, assuming an R
^2^ value of 0.5 and 8 parameters in the model. It would also allow the estimated R
^2^ value to be within recommended limits of 0.05 of the true R
^2^ value. It would allow the estimation of residual standard deviation to be within 13%. Although this is above the recommended 10%, we believe that it is still clinically meaningful. It also allows the estimation of the mean outcome to within +/- 1.5%, which is sufficiently precise to be clinically useful, assuming an overall mean of 14 and an SD of 13. This represents 18.75 individuals per variable, which is within the traditional 10–20 individuals per variable rule-of-thumb. The analysis will be based on traditional regression methods and follow the Transparent reporting of a multivariable prediction model for individual prognosis or diagnosis (TRIPOD) statement
^
16
^. An outline of the analysis is as follows:

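### The rule on who enters the analysis has no final-diagnosis condition and contradicts the MPE-only population stated elsewhere in the protocol

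*Protocol article*

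**What the plan says.** Three places in the protocol article bear directly on who is analysed.

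- **Inclusion in analysis** (Statistics and data analysis): "All participants with available data will be included in the day seven analysis". The next sentence reads "For the one month and three-month outcomes, all participants including those lost to follow-up or who die within the time period will be included". The only condition at day seven is that data exist. Final diagnosis is not mentioned at any time point.
- **Data from feasibility study** (Introduction): "We plan to analyse data only on patients with a final diagnosis of an MPE". The reason given is that "effusions from other causes usually resolve with treatment of the underlying cause and recurrence is not a problem". The same section sets the Phase 1 target: 200 recruited, so that at least 150 have both a final diagnosis of MPE and the full primary outcome.
- **Sample size and analysis plan**: "approximately 20% of patients will turn out not to have MPE and therefore will not be eligible for inclusion in the final analysis". This section also places the primary outcome at one week, so the day-seven analysis is the primary one.

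The section Objectives and outcome measures states the primary objective for patients with MPE. The inclusion criteria admit known or suspected malignancy, so some enrolled patients will prove not to have MPE.

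**The concern.** The protocol states two different populations for its primary analysis. The difference matters because the protocol itself says that non-malignant effusions follow another course, which is its reason for leaving them out. If an analyst followed Inclusion in analysis to the letter, a score meant for patients with MPE would be developed partly on patients without it. The candidate predictors include type of malignancy, whether malignancy was already known, and pleural fluid cytology. In a mixed cohort these could gain weight by telling benign from malignant fluid rather than by predicting reaccumulation within MPE.

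This is not a detail left to an analysis plan or lost when the protocol was condensed into an article. The article states both rules, and they do not agree.

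**Working it through.** **1. Does the sample size rest on the MPE-only population?**

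Inputs from Sample size and analysis plan: n = 150, p = 8 parameters, R² = 0.5, SD = 13. The standard criteria for a continuous-outcome prediction model are:

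- Shrinkage: S = 1 + (p − 2) / (n · ln(1 − R²app)), with R²app = (R²(n − p − 1) + p) / (n − 1). At n = 150, R²app = (0.5 × 141 + 8) / 149 = 0.527 and S = 0.9465.
- Optimism in R²: p(1 − R²) / (n − 1) = 8 × 0.5 / 149 = 0.027.
- Residual SD: the larger 95% chi-square margin on n − p − 1 = 141 degrees of freedom.
- Mean outcome: half-width t × 13 × √(0.5 / n).

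| Quantity | Protocol states | n = 150 | n = 200 |
|---|---|---|---|
| Shrinkage factor | 0.95 | 0.9465 | 0.959 |
| Optimism in R² | within 0.05 | 0.027 | 0.020 |
| Residual SD, within | 13% | 13.2% | 11.1% |
| Mean outcome, ± | 1.5 | 1.48 | 1.28 |
| Participants per variable | 18.75 | 150/8 = 18.75 | 200/8 = 25 |

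The stated figures reproduce at 150. They do not describe an analysis of 200.

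**2. How do 200 recruits become 150 analysed?**

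In the feasibility study 12 of 15 aspirated patients had malignancy, so 3/15 = 20% did not. Then 200 × 0.80 = 160 with MPE, and 150/160 = 0.9375, which leaves about 6% for missing data and other losses. This fits the statement that non-MPE diagnoses are the main reason for the shortfall. Without the diagnosis exclusion, the planned step from 200 to 150 is not explained.

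**3. What does Inclusion in analysis permit if read literally?**

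Up to 200 participants at day seven, of whom up to 200 × 0.20 = 40 would not have MPE. At the same rate, up to 40 × 0.20 = 8 of the validation cohort would not.

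**4. Does another section supply the missing condition?**

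The exclusion criteria remove known transudates, pleural infection, and effusions clinically thought to be primarily cardiac, renal or hepatic. A benign effusion of unknown cause can still be enrolled. The withdrawal section keeps data collected before withdrawal in the analysis unless the participant asks otherwise, or loses capacity without having agreed to retention. It does not restrict by final diagnosis either.

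**The case against.** The strongest reply is that Inclusion in analysis concerns completeness of data, not diagnosis. It follows directly on the section about missing data, loss to follow-up and death. It contrasts day seven (those with data) with the later time points (everyone, including those lost or dead). On that reading participants means those already eligible, and the sample size section, a little earlier in the same statistics chapter, has settled eligibility by diagnosis. An analyst would have to disregard the feasibility section, the objective and the sample size section to fit the model on non-MPE patients.

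Much of this stands. The reading is plausible, the intended population can be recovered, and Inclusion in analysis is not the only place where the population is described. But the section carries no such limit, missing data already have a section of their own, and the second sentence again says all participants. The wording still conflicts with the other two sections.

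A reader might go further and infer that R² would be inflated and the score miscalibrated. The documents do not support that. As an illustration, assume 20% non-MPE, a within-group SD of 13, and a mean change d points lower in non-MPE patients. The split's share of outcome variance is 0.2 × 0.8 × d² / (169 + 0.2 × 0.8 × d²):

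- d = 5: 4.0/173.0 = 2.3%
- d = 10: 16.0/185.0 = 8.6%
- d = 14: 31.4/200.4 = 15.7%

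No value of d is given in the protocol. These shares are ceilings, reached only if the predictors separate the groups perfectly. If the stated mean of 14 is the MPE mean, d = 14 would mean no average reaccumulation in non-MPE patients. Day seven is also the visit at which fluid results are given and management is decided, so a large effect of treating the cause by then is doubtful. Pooling groups with different predictor–outcome relations can also lower R².

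**Conclusion.** The contradiction is real and concerns the primary analysis population. Inclusion in analysis is wrong as written. The MPE-only rule is the intended one, because the feasibility section, the objective and the sample size section agree on it and the stated precision figures belong to 150 patients.

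Read literally, the rule admits up to about 40 of 200 patients from outside the target population. That is an upper bound. It assumes that the 20% rate from the feasibility study holds, that every participant has day-seven data, and that the two contrary statements are ignored. It should not be read as a forecast that the score will be built on 160 MPE and 40 non-MPE patients. The effect on R² and calibration is undetermined in both size and direction. The sample-size calculation needs no change on this account.

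The correction is worth making before analysis because it removes a choice of primary population at no cost. It does not call the design into question.

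**What to change.** Reword Inclusion in analysis along these lines: *The day-seven analysis will include all participants with a final diagnosis of MPE and available day-seven data. The one- and three-month analyses will include all participants with a final diagnosis of MPE, including those lost to follow-up or who die within the period.*

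State that the same restriction applies to the 40-patient validation cohort. No text about that cohort conflicts with this; the addition is for consistency. If an analysis of all participants is wanted, label it a sensitivity analysis.

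No separate aspiration condition is needed. The feasibility section says the revised entry criteria ensure that enrolled patients are aspirated, and inability to aspirate is already listed among the withdrawal reasons.

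The cost is a short rewording, with no additional patients, visits or data.

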**Assessment of effusion size on CXR**
*

Percentage opacification of the hemithorax by effusion will be measured on the post-procedure and follow-up CXR. This is a validated measure of effusion size performed using freely available software (
PaintShop Pro 2022 (RRID:SCR_000338), Corel Corporation and
ImageJ version 1.53r (RRID:SCR_003070),
National Institutes of Health (RRID:SCR_011417)). Anonymised digital CXR images will be uploaded onto the study database. PaintShop Pro is used to outline the hemithorax and effusion. These shapes are then converted into a pixel count by ImageJ. Percentage opacification is calculated by dividing the effusion pixel count by the hemithorax pixel count. This analysis takes approximately five minutes per image.

### Data management

**
*Source data*
**

Source documents are where data are first recorded, and from which participants’ CRF data are obtained. These include, but are not limited to, hospital records (from which medical history and previous and concurrent medication may be summarised into the CRF), clinical and office charts, laboratory and pharmacy records, diaries, microfiches, radiographs, and correspondence.

CRF entries will be considered source data if the CRF is the site of the original recording (
*e.g.*, there is no other written or electronic record of data). All documents will be stored safely in confidential conditions. On all study-specific documents, other than the signed consent, the participant will be referred to by the study participant number/code, not by name.

*
**Access to data**
*

Direct access will be granted to authorised representatives from the Sponsor, host institution and the regulatory authorities to permit study-related monitoring, audits and inspections. Data will be made available as an online supplement at the time of publication.

*
**Data recording and record keeping**
*

All study data will be entered on to a web-based data management system (
REDCap (RRID:SCR_003445)).

The study database is bespoke and hosted on the University of Oxford server with services provided through Oxford University Medical Sciences Division IT Services. The server and database are protected by a number of measures including anti-virus and anti-spyware applications, firewalls, encryption technology and permissions. The database will be backed up on a daily basis. The Data Manager will maintain a list of personnel with authorization to edit and/or view data. All study data will be archived for five years.

The database and access to computers are password protected. Paper-based identifiable data at each site will be kept in a locked cabinet, in a locked or ID-access controlled area this will be kept for 6–12 months post the end of the study only if the participant consents to being informed of the study results. If participants do not consent to this, identifiable information will be destroyed once data analysis has taken place.

The participants will be identified by a unique trial specific number in any database. The name and any other identifying detail will not be included in any study data electronic file.

### Quality assurance procedures

The study will be conducted in accordance with the current approved protocol, principles of GCP, relevant regulations and standard operating procedures. The Trial Management Committee (consisting of the trial manager and chief investigator) will meet monthly to ensure the trial is running as planned.

Regular monitoring will be performed according to principles of GCP. Data will be evaluated for compliance with the protocol and accuracy in relation to source documents. Following written standard operating procedures, the monitors will verify that the clinical study is conducted, and data are generated, documented and reported in compliance with the protocol, principles of GCP and the applicable regulatory requirements.

### Ethical and regulatory considerations

**
*Declaration of Helsinki*
**

The Investigator will ensure that this study is conducted in accordance with the principles of the Declaration of Helsinki.

*
**Guidelines for GCP**
*

The Investigator will ensure that this study is conducted in accordance with relevant regulations and principles with GCP.

*
**Approvals**
*

The protocol, informed consent form and participant information sheet have been submitted to an appropriate Research Ethics Committee (REC), and written approval was given on 15
^th^ June 2021 (Ethics Ref: 21/PR/0607; IRAS Project ID: 295614).

The Investigator will submit and, where necessary, obtain approval from the above parties for all substantial amendments to the original approved documents.

*
**Reporting**
*

The Chief Investigator shall submit once a year throughout the clinical study, or on request, an Annual Progress Report to the REC, host organisation and Sponsor. In addition, an End of Study notification and final report will be submitted to the REC, host organisation and Sponsor.

*
**Participant confidentiality**
*

The study staff will ensure that the participants’ anonymity is maintained. The participants will be identified only by a participant ID number on all study documents and any electronic database, with the exception of the CRF, where participant initials may be added. All documents will be stored securely and only accessible by study staff and authorised personnel. The study will comply with the Data Protection Act, which requires data to be anonymised as soon as it is practical to do so.

*
**Expenses and benefits**
*

All visits are part of standard clinical care so no travel expenses will be offered to patients.

### Coronavirus disease 2019 (COVID-19) risk mitigation

In the light of the current COVID-19 pandemic, it is essential that research participants and staff are kept safe and not exposed to any unnecessary risk. The participants eligible for enrolment into REPEAT are a high-risk group, because they may have disseminated cancer (albeit undiagnosed at the time of recruitment). REPEAT has been designed to align with standard clinical care. The participant will have two face-to-face hospital visits, one for initial pleural fluid drainage and the second for results and reassessment. Both are essential visits. All other follow-up visits can be done by telephone. All staff and participants will wear masks, practice social distancing where possible and perform good hand hygiene, all as standard care. Therefore, the participants or staff will not be exposed to any increased risk of COVID-19 infection while participating in REPEAT.

A further risk from COVID-19 is to the recruitment success of the trial. Recruitment will start in the second quarter of 2021, by which time we anticipate coming to the end of the predicted Winter peak of COVID-19 infections. Therapeutic aspiration is an essential, emergency procedure that prevents hospital admission. Therefore, Pleural Clinics have continued to provide this procedure during the COVID-19 pandemic, and we anticipate this will continue. Thus, we do not predict a decrease in pleural procedures due to COVID-19.

Finally, there is the risk of lack of availability of research staff to support recruitment and data collection. However, the recruiting centres all integrate their research and clinical teams, and we anticipate that we will be able to recruit successfully.

**Insurance**
*

NHS bodies are legally liable for the negligent acts and omissions of their employees. If subjects are harmed whilst taking part in a clinical study as a result of negligence on the part of a member of the study team this liability cover would apply.

Non-negligent harm is not covered by the NHS indemnity scheme. The Norfolk and Norwich University Hospital NHS Foundation Trust, therefore, cannot agree in advance to pay compensation in these circumstances.

In exceptional circumstances an
*ex-gratia* payment may be offered.

### Publication policy

Once completed, this study will be submitted to a conference as an abstract and as a paper to a peer-reviewed journal.

## Study status

As of 24
^th^ June 2022, five sites are currently recruiting to the study and 62 subjects have been recruited. Five more sites are currently in set up.

## Data Availability

No data are associated with this article. Extended data Zenodo: REPEAT protocol extended data.
https://doi.org/10.5281/zenodo.7551597
^
16
^ This project contains the following extended data: - Full_CRF_pack.pdf - REPEAT_Consent_form_WithSamples_V2.0_28May2021_NNUH.doc - REPEAT_PIS.docx - REPEAT therapeutic aspiration SOP.docx - REPEAT ultrasound SOP.docx - REPEAT_VAS_diary.pdf Data are available under the terms of the Creative Commons Attribution 4.0 International license (CC-BY 4.0).
